
### Interim analyses {21b}

Because this study was designed to confirm the non-inferiority of a dose reduction of an already effective drug, it was highly unlikely that the primary endpoint would be significantly improved or worsened compared to controls.

### Methods for additional analyses (e.g., subgroup analyses) {20b}

There are no plans to conduct subgroup analyses. In case there are any modifications to the original statistical analysis plan, the plan itself and, if necessary, the research protocol will be updated accordingly. The summary report of the study will include an explanation of the updated sections and the reasons for the changes made to the statistical analysis plan.

### Methods in analysis to handle protocol non-adherence and any statistical methods to handle missing data {20c}

In terms of protocol compliance, the following cases are considered as part of the discontinuation criteria: poor drug adherence (less than 70% or more than 120% of the total scheduled doses), the inability of the patient to come to the hospital due to relocation or other reasons, and the inability to administration of relugolix for more than 8 weeks.

### Plans to give access to the full protocol, participant-level data, and statistical code {31c}

The principal investigator shall prepare a primary endpoint report (a document summarizing the results of data collection for the primary endpoint) and a summary report (a document summarizing the results of the relevant clinical research) and its summary within the following period, and publish them by recording them in the jRCT.Primary endpoint report: to be prepared and published in principle within 1 year after the end of the period for collecting data on the primary endpoint.Summary report and its summary: to be prepared and published in principle within 1 year after the end of the period for collecting data on all endpoints.

Full protocol can be provided upon request, but participant-level data and statistical code will be provided through anonymization after approval by the ethics review board.

### Oversight and monitoring

#### Composition of the coordinating center and trial steering committee {5d}

The facility administrator should receive periodic reports regarding the implementation plan, the decision on whether or not to conduct the study, opinions from the Certified Review Board (CRB), reporting adverse events and other illnesses (including serious illnesses) that may have a causal relationship with the research, periodic reporting every year and within 2 months after the end of each relevant period, primary endpoint report and summary report preparation, summary report public availability, and public disclosure of the summary report. The CRB is an organization approved by the Ministry of Health, Labor and Welfare. Its roles include evaluating and approving the research protocol, inspecting source documents, reporting adverse events and other illnesses (including serious illnesses) that may have a causal relationship with the research, submitting periodic reports annually and within 2 months after the relevant period has expired, submitting noncompliance reports, making recommendations for deviations from the research protocol, or revising or discontinuing the study.

#### Composition of the data monitoring committee, its role, and reporting structure {21a}

Monitoring will be conducted to confirm that the study is being conducted safely and in accordance with the protocol and that data is being collected accurately. The details of monitoring (method, timing, content, etc.) will be specified in the “Procedures for Monitoring” and conducted in accordance with the “Monitoring Plan.” Monitoring will be conducted by a specialist who is not directly involved in the conduct of the study at the site, in accordance with the “Procedures for Monitoring” and the “Monitoring Plan.”

#### Adverse event reporting and harms {22}

The safety endpoints in this study are as follows: (1) depression during the trial with the relugolix by which it is most likely caused, (2) hepatic dysfunction (aspartate aminotransferase [AST]/alanine aminotransferase [ALT] levels) indicated as grade 4 by Common Terminology Criteria for Adverse Events (CTCAE) v5.0 during treatment with the relugolix, (3) angina pectoris with the relugolix, and (4) severe anemia indicated as grade 4 by CTCAE v5.0 during treatment with the relugolix. Depression is a relatively common side effect, occurring in less than 1% of patients, but will be considered less common in this trial because half of the participants will be administered a half dose approved by the Ministry of Health, Labor and Welfare in Japan. In the event of the above adverse reaction, the patient will be promptly examined and treated by a medical specialist, and a decision will be made whether to discontinue the trial or not, taking the participant’s wishes into consideration. The administrator of the institution will be notified, and the case will be reported to an accredited clinical research review committee. Although the frequency of hepatic dysfunction is not revealed but has also been reported, then the same measures will be taken. This clinical research does not include information about genetic characteristics that can be passed on to subjects or their offspring.

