## Introduction

### Background and rationale {6a}

Uterine leiomyomas are commonly detected with a prevalence reaching up to 60% of reproductive-aged women [1, 2] and affect women’s quality of life due to heavy menstrual bleeding or dysmenorrhea [3–5]. Leiomyomas grow according to estradiol exposure and decrease after post-menopause [6, 7]. In clinical practice, pharmacotherapy or surgical treatment is proposed for serious symptoms like abdominal distension, dysuria, infertility, or severe anemia due to heavy menstrual bleeding caused by leiomyomas. In the case of pharmacotherapy, a gonadotropin-releasing hormone (GnRH) receptor agonist (i.e., leuprorelin acetate or goserelin acetate) has been used to pause the menstrual cycle [8]. However, it induces a transient increase in gonadotropins and sex hormones, resulting in a clinical flare-up or temporary worsening of symptoms, and typically takes about 4 weeks to achieve a therapeutic effect [3, 9]. GnRH receptor antagonists (i.e., relugolix, elagolix, or linzagolix) are also used as newer treatments for uterine leiomyomas [10, 11]. Relugolix is a new orally active small molecule GnRH receptor antagonist [12–14] which proved its sufficient efficacy to suppress estradiol without the transient estradiol flare-up compared with GnRH agonist [15, 16]. However long-term administration should not be permitted liable to for climacteric disorder or osteoporosis. In the case of surgical treatment, pharmacotherapies like GnRH agonists or antagonists aimed at the reduction of leiomyoma and uterine volume or improvement of anemia are also introduced before the surgical treatment to conduct less invasive surgery (i.e., to reduce blood loss or surgical duration). However, the clinician often encounters cases in which menopausal symptoms are thought to be drug-related at about 8 weeks after the beginning of treatment, making it difficult to continue treatment [17]. Since the phase III trial was designed for relugolix administration to patients with leiomyoma, the leiomyoma volume as a secondary endpoint was reduced by 43.28 ± 33.85% by 12 weeks and 49.75 ± 34.33% by 24 weeks of administration compared with the baseline; we have hypothesized that everyday administration for 8 weeks and subsequently every-other-day administration of relugolix only for maintaining the effect could be a compatible method [18].

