#### Criteria for discontinuing or modifying allocated interventions {11b}

The criteria for discontinuing are as follows: (1) If the subject declines to participate in the study or withdraws consent; (2) If the subject is found to be ineligible after enrollment; (3) If the primary illness is completely cured by emergency surgery or other means and there is no longer a need for continued administration; (4) If the subject has persistent heavy genital bleeding due to deterioration of the primary illness and anemia of grade 3 or higher as defined in CTCAE v5.0 Grade; (5) The following serious adverse reactions associated with study drug administration are observed. Depression: when the patient does not respond to psychiatric treatment and the main cause is considered to be the study drug. Hepatic dysfunction: AST/ALT levels of grade 2 or higher in the CTCAE v5.0 Grade definition. Angina pectoris: diagnosed during the period of study drug administration; (6) Exacerbation of side effects associated with study drug administration that makes continuation of study drug administration inadvisable; (7) If the subject develops hypersensitivity to the study drug itself; (8) If the subject becomes pregnant; (9) If the subject’s medication adherence is extremely poor or over (< 70% of the total scheduled doses or > 120% of the total scheduled doses); (10) The subject fails to come to the hospital due to relocation or other reasons and is unable to receive relugolix for more than 8 weeks; (11) The entire study is terminated; (12) The physician deems it appropriate to terminate the subject’s continued participation in the study for other reasons; and (13) If the subject has any of the following serious adverse reactions to the study drug.

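### The liver and anaemia safety endpoints count only grade 4, above the protocol's own stopping grades, and the stopping instruction for liver events is discretionary in one section and a listed criterion in another

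*Protocol article*

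**What the plan says.** The protocol article names four safety endpoints under Adverse event reporting and harms {22}. Depression and angina carry no grade. The liver endpoint is "hepatic dysfunction (aspartate aminotransferase [AST]/alanine aminotransferase [ALT] levels) indicated as grade 4 by Common Terminology Criteria for Adverse Events (CTCAE) v5.0", and the anaemia endpoint is "severe anemia indicated as grade 4 by CTCAE v5.0 during treatment with the relugolix". The liver endpoint is likewise confined to the time on relugolix.

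The Criteria for discontinuing or modifying allocated interventions {11b} use lower grades. Among serious reactions associated with the study drug they list "Hepatic dysfunction: AST/ALT levels of grade 2 or higher in the CTCAE v5.0 Grade definition" and "Angina pectoris: diagnosed during the period of study drug administration". A separate item covers "persistent heavy genital bleeding due to deterioration of the primary illness and anemia of grade 3 or higher as defined in CTCAE v5.0 Grade". Depression is a criterion only after psychiatric treatment has failed and the drug is thought to be the main cause.

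On what to do when an event occurs, {22} says that "a decision will be made whether to discontinue the trial or not", with the participant's wishes weighed. It then adds: "Although the frequency of hepatic dysfunction is not revealed but has also been reported, then the same measures will be taken". Plans to promote participant retention and complete follow-up {18b} gives the principal investigator the same discretion for severe adverse effects related to relugolix. Section {11d} on concomitant care allows the drug to continue with supportive treatment for abnormal liver function and names no grade limit.

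**The concern.** Safety is part of the stated objective in {7}, and the abstract's discussion speaks of superiority in reducing adverse effects. A named safety endpoint should then at least contain the events that the protocol treats as reason enough to stop the drug. For liver events and bleeding-related anaemia it does not. A count by arm of these two endpoints would say less about harm than the collected data allow.

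The stopping wording matters in practice. A physician with a grade 4 ALT result attributed to relugolix finds a discontinuation criterion in {11b} and a choice in {22} and {18b}. The trial is open-label ({17a}), so physicians who resolve this differently do so knowing the arm.

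**Working it through.** The plan gives no figure on this point, and no rates of liver events or anaemia by grade. The check is therefore a comparison of the sections, with simple counting of grades.

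**Step 1: grades.**

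| Safety endpoint in {22} | Counted at | Stopping criterion in {11b} | Ends treatment but is not counted |
|---|---|---|---|
| Liver (AST/ALT) | grade 4, on treatment | grade 2 or higher, drug-associated | grades 2 and 3 (4 − 2 = 2 grades) |
| Anaemia | grade 4, on treatment | grade 3 or higher with persistent heavy bleeding | grade 3 with such bleeding (4 − 3 = 1 grade) |
| Angina | any | any diagnosis on drug, drug-associated | none |
| Depression | any, if relugolix is the most likely cause | unresponsive to psychiatric treatment, drug the main cause | none |

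The grade gap affects 2 of the 4 endpoints. A patient stopped at grade 2 or 3 who later worsens is off drug, so the later grade 4 value also falls outside the on-treatment window.

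**Step 2: what is still captured.** Adverse effects are checked at every visit (Table 1) and monthly ({18a}), and the data center is told of each discontinuation ({19}). The events are on record. Scheduled laboratory tests fall before treatment, at 8 weeks and after 24 weeks ({18a}), so a grade 4 value can be the first abnormal one seen.

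**Step 3: stopping instruction, event by event.**

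- *Liver.* {22} extends its case-by-case measures to hepatic dysfunction by name. {11b} lists AST/ALT of grade 2 or higher, subject only to the lead-in that the reaction is associated with the drug. Once that attribution is made, the two sections give different instructions.
- *Angina.* {11b} lists it under the same lead-in. {22} refers back to the reaction above in the singular, directly after a sentence about depression alone, and then extends the measures to the liver only. The conflict exists if that back-reference covers all four endpoints, or if the angina is a severe adverse effect under {18b}; otherwise it does not.
- *Anaemia.* Grade 4 without persistent heavy bleeding meets no specific grade criterion in {11b}, so discretion is appropriate. With such bleeding, a conflict depends on the same reading as for angina.
- *Depression.* Consistent, because the {11b} criterion is itself conditional.

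The result is one clear conflict (liver), two conditional ones (angina, and grade 4 anaemia with heavy bleeding) and none for depression.

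**The case against.** The strongest reply on the grades is that a stopping rule exists to prevent the severe event, so it should sit below it, and that {22} is a list for specialist referral and expedited reporting, for which grade 4 is a natural bar. For anaemia there is a further reason: the disease itself produces "severe anemia due to heavy menstrual bleeding caused by leiomyomas", and iron is permitted on study ({11d}). It is true that the two thresholds need not be equal and that this is not a logical contradiction. But {22} calls these items safety endpoints, not only reporting triggers, and {11b} places AST/ALT of grade 2 or higher among serious adverse reactions. The anaemia argument does support tying grade 3 to heavy bleeding instead of counting every grade 3 value.

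On stopping, one can say that {11b} concerns the drug and {22} concerns remaining in the trial. That reading is possible, but {11b} mixes drug withdrawal and study withdrawal in one list, so it does not clearly reconcile the sections. The causality lead-in in {11b} does leave room for judgement, which the specialist examination in {22} could supply. It explains discretion over attribution, but not discretion after attribution. The last item of {11b} announces a list that does not follow, so the full protocol may say more; the conflict shown here lies in text that the article does state.

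A reader might infer that these harms go unrecorded or that the grade 4 endpoints must stay empty. Step 2 of the check shows that neither follows. Nor does the text support a flat statement that stopping for angina is discretionary.

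**Conclusion.** The point holds and is minor. Two of four named safety endpoints leave out events that the protocol itself treats as grounds for stopping: two AST/ALT grades, and one anaemia grade when heavy bleeding is present. The stopping instruction is in conflict for drug-attributed liver dysfunction, and for angina only under the readings set out above.

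This rests on reading the {22} decision as one about the individual patient, which its reference to her wishes supports, and on {11b} being a list of criteria. The document does not call them mandatory, and the point does not need that. No number of uncounted events is claimed.

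A reader might go further and conclude that the trial's side-effect comparison is compromised. It is not: {20a} plans no test on these four endpoints, and the comparisons of the Kupperman Index, bone mineral density and serum BAP do not depend on them.

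**What to change.** In {22}, define the hepatic safety endpoint as on-treatment AST/ALT of CTCAE grade 2 or higher. Define the anaemia endpoint to include at least grade 3 or higher with persistent heavy genital bleeding, plus any grade 4. In both, count events that lead to discontinuation and report the worst grade by arm.

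In {22} and {18b}, state that the {11b} criteria govern stopping of study drug. Keep case-by-case discretion for the causality assessment and for events that meet no {11b} criterion.

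The cost is a few sentences and one table built from adverse-event, discontinuation and laboratory data already collected, with no new visits or tests. The downside is a larger number of counted safety events.

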**Methods:**

A minimization adaptive randomized control trial (RCT) will be conducted. Patients (over 20 years old) harboring leiomyoma who will be undergoing surgical treatment will be invited to participate. Patients who are enrolled in the intervention group will receive every-other-day administration for 16 weeks after 8 weeks of daily administration. Patients who are enrolled in the control group will receive daily throughout the 24 weeks. The primary outcome is the leiomyoma volume reduction, and the secondary endpoints are the reduction of uterine volume, the occurrence of the climacteric disorder, genital bleeding days, change rate of serum hormone or bone turnover markers, and bone mineral density after 24 weeks compared to before administration.

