#### Intervention description {11a}

The initial dose of relugolix is 40 mg orally once daily before meals, starting on days 1–5 of the menstrual cycle until day 56. On day 57, the control group will continue taking 40 mg of relugolix every day, and the intervention group will switch to 40 mg of relugolix every other day. However, change to another group will not be permitted.

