### Assignment of interventions: blinding

#### Who will be blinded {17a}

This is an open-label trial.

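### The depression safety endpoint counts only cases attributed to relugolix, a judgement open to influence by knowledge of the arm in this open-label trial; the half-dose wording beside it also needs reconciling (minor)

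*Protocol article*

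**What the plan says.** Adverse event reporting and harms {22} lists four safety endpoints. The first is "depression during the trial with the relugolix by which it is most likely caused". Hepatic dysfunction and severe anemia, in the same list, are defined by CTCAE v5.0 grade 4 during treatment, with no condition on cause. The section puts the frequency of depression as a side effect at below 1%. It expects fewer cases in this trial because "half of the participants will be administered a half dose approved by the Ministry of Health, Labor and Welfare in Japan", and sets no time limit on that statement.

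On blinding, section {17a} states: "This is an open-label trial". Sequence generation {16a} has attending physicians who take part in the intervention enter all outcome data in the case report form, with the data analysts blinded. Outcomes {12} has the MRI volumes read blind by a radiologist at another hospital.

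On the regimen, Intervention description {11a} says for both arms: "The initial dose of relugolix is 40 mg orally once daily before meals, starting on days 1–5 of the menstrual cycle until day 56". It continues: "On day 57, the control group will continue taking 40 mg of relugolix every day", while "the intervention group will switch to 40 mg of relugolix every other day". The abstract gives the intervention as "every-other-day administration for 16 weeks after 8 weeks of daily administration".

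**The concern.** An endpoint that admits an event only after someone has judged its cause is only as objective as that judgement. Here whoever judges can know the arm, and the same section records in advance an expectation that links lower dose to less depression. An episode in a patient on daily dosing could be attributed to the drug more readily than the same episode in a patient dosed every other day. An event judged unrelated drops out of the endpoint altogether.

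The blinding that the article describes does not reach this step. Blinded MRI reading protects the volume endpoints. Blinded analysts receive an event list that has already been filtered.

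At stake is how far the depression count can support the safety evaluation named in Objectives {7} and the abstract's aim of showing fewer adverse effects. With so few events expected, reclassifying one case could change the impression the table gives.

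The dose statement is a separate and smaller matter. Read as written, it describes a larger reduction in exposure than the regimen sections produce.

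**Working it through.** **1. What each safety endpoint requires ({22})**

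| Endpoint | Condition for counting | Causality judgement needed |
|---|---|---|
| Depression | relugolix the most likely cause | yes |
| Hepatic dysfunction | AST/ALT, CTCAE grade 4, during treatment | no |
| Severe anemia | CTCAE grade 4, during treatment | no |

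The authors therefore already define two endpoints in the list without attribution. For depression, {22} does not say who judges the cause. It does say that a medical specialist examines and treats the patient, but not that the specialist is unaware of the arm.

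**2. Scheduled dose**

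Inputs: 40 mg per dose; control daily for 24 weeks ({6b}); intervention daily for 8 weeks, then every other day for 16 weeks ({11a} and abstract).

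- Control: 24 × 7 = 168 doses; 168 × 40 = 6,720 mg.
- Intervention: 8 × 7 + (16 × 7)/2 = 56 + 56 = 112 doses; 112 × 40 = 4,480 mg.
- Weeks 1–8: 56/56 = 1.00 of control.
- Weeks 9–24: 56/112 = 0.50 of control.
- Whole course: 112/168 = 0.667 of control.
- Average over both arms: (168 + 112)/(2 × 168) = 0.833 of all-daily dosing, against (1 + 0.5)/2 = 0.75 if one arm had half throughout.

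One half is reproduced for weeks 9–24 only.

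**3. How many events are involved**

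The section gives only an upper bound of 1%. I take 0.2% to 1% as an assumed range, with 70 patients per arm. For the reduced arm I assume, for illustration, that risk is proportional to dose.

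| Rate on daily dosing | All 140 on daily dosing | One arm at 2/3 | One arm at 1/2 |
|---|---|---|---|
| 1% | 140 × 0.01 = 1.40 | 0.70 + 0.47 = 1.17 | 0.70 + 0.35 = 1.05 |
| 0.2% | 140 × 0.002 = 0.28 | 0.14 + 0.09 = 0.23 | 0.14 + 0.07 = 0.21 |

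The choice between one half and two thirds moves the expected count by 1.17 − 1.05 = 0.12 event at most. The chance of no case at all under full dosing is 0.99^140 = 0.24 at 1% and 0.998^140 = 0.76 at 0.2%.

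**4. How far differential attribution could move the count**

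Hold attributed cases in the daily arm at the 1% ceiling: 70 × 0.01 = 0.70. Suppose 80% of episodes are attributed there (assumption). The true all-cause rate is then 1%/0.8 = 1.25%, or 70 × 0.0125 = 0.875 episodes, taken as equal in both arms.

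- 80% attributed in the other arm: 0.70 against 0.70, gap 0.
- 50% attributed: 0.875 × 0.5 = 0.44, gap 0.26.
- None attributed: gap 0.70.

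Under these assumptions the artefact is below one event even at the extreme.

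**The case against.** The other side has a good deal to say.

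- **The dose wording is imprecise, not wrong in direction.** One half is the correct dose rate in the only period when the arms differ. Lower exposure holds at two thirds as well, and the sentence feeds no sample size, margin or test. This stands. The arithmetic gives no reason to delete the expectation of fewer cases.
- **No formal comparison rests on the count.** Section {20a} plans no between-group test of depression. The closing paragraph of the Discussion ties superiority to the secondary endpoints, which in {12} are uterine volume, Kupperman score, bone mineral density and serum BAP. This stands, and it limits the consequence.
- **Depressive symptoms are also captured without attribution.** The Kupperman Index includes melancholia and nervousness and is taken before treatment and at 8 and 24 weeks ({18a}). Adverse effects are checked monthly. This helps, but the index is completed open-label and is not a diagnosis of depression.
- **The article is condensed.** Causality fields and full adverse-event tables may sit in documents not shown. That is fair for the tabulations, but the endpoint definition is stated here, and the causality condition is part of it.

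Two stronger readings are not supported. A reader might infer that the endpoint is biased and that the dose expectation is built into it. The definition and the expectation are separate statements, no attribution rule by arm is given, the person who assesses causality is not named, and a specialist sees the patient. The text shows openness to bias and no more.

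A reader might also see a conflict with section {11b}, which has depression lead to discontinuation "when the patient does not respond to psychiatric treatment and the main cause is considered to be the study drug". That is a discontinuation criterion. A threshold for stopping that is narrower than a reporting endpoint is not a contradiction.

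**Conclusion.** The point holds as a minor one. The depression endpoint carries a causality filter that knowledge of the arm can influence, while two neighbouring endpoints do not, and no blinded causality assessment is described. Separately, the unqualified half-dose statement in {22} does not agree with the abstract, {6b} and {11a}, which together give 67% of the control total over 24 weeks and no difference to day 56.

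The practical size is small. At the ceiling of 1%, between 1.2 and 1.4 cases are expected in the whole trial, depending on whether risk falls with dose. The fraction used changes this by about 0.1 event, and differential attribution by less than one. These figures rest on the section's own bound of below 1%, the assumed lower rate of 0.2%, proportional risk, and the illustrative attribution shares. A higher true rate would make the filter matter more, but nothing in the document supports one.

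**What to change.** 1. Define the endpoint as any new or worsened depression during treatment, whatever its judged cause. Tabulate it by arm and by period (to day 56, and from day 57).
2. Record the causality judgement as a separate item and report the drug-related subset beside the full count, so that nothing now planned is lost.
3. Reconcile the dose statement in {22} with the abstract, {6b} and {11a}, so that the reader can tell which period it refers to and what share of the control total it implies.

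The cost is wording in the protocol and the case report form, with no change to sample size or visits. The downside is that a few events unrelated to the drug will be counted.

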#### Relevant concomitant care permitted or prohibited during the trial {11d}

Since relugolix is a substrate of p-glycoprotein, concomitant use of erythromycin, which inhibits p-glycoprotein, or rifampicin, which induces p-glycoprotein, increases or decreases the blood concentration of relugolix, so these drugs will be restricted to concomitant use during the study period. Patients will be carefully monitored for adverse reactions to the study drug by interview and examination, and the study drug will be continued under supportive care. Supportive care includes antidepressants for depression, hepatotropic agents (ursodeoxycholic acid or stronger neo-minophagen C) for abnormal liver function, oral hemostatic agents (carbazochrome sodium sulfonate hydrate and tranexamic acid) for irregular vaginal bleeding, and iron intravenous and oral administration of iron for iron deficiency anemia associated with illicit genital bleeding are acceptable.

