#### Plans to promote participant retention and complete follow-up {18b}

Patients visit our hospital monthly, and each attending physician fills out the CRF. Revealed with severe adverse effects related to the administration of relugolix, the attending physician will examine and consult a specialist, and the principal investigator will decide whether to discontinue the trial or not, taking the participant’s wishes into consideration. The administrator of the institution will be notified, and the case will be reported to an accredited clinical research review committee. Compensation insurance will be purchased to compensate for any health problems that may occur to research subjects in relation to the clinical research. In preparation for liability, the principal investigator will purchase liability insurance.

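### {11b} requires relugolix to stop at drug-related AST/ALT of grade 2 or higher, but {22} leaves hepatic dysfunction, grade 4 included, to a case-by-case decision not made subject to {11b}

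*Protocol article*

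**What the plan says.** Four places in the protocol article bear on liver events.

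- **{11b}, criteria for discontinuing.** Item 5 is introduced by "The following serious adverse reactions associated with study drug administration are observed" and includes "Hepatic dysfunction: AST/ALT levels of grade 2 or higher in the CTCAE v5.0 Grade definition".
- **{22}, adverse event reporting and harms.** AST/ALT elevation is a safety endpoint when it is "indicated as grade 4 by Common Terminology Criteria for Adverse Events (CTCAE) v5.0 during treatment with the relugolix". After a comment on depression, the section says that the patient will be examined and treated by a specialist and that "a decision will be made whether to discontinue the trial or not", with the patient's wishes taken into account. It then adds: "Although the frequency of hepatic dysfunction is not revealed but has also been reported, then the same measures will be taken".
- **{18b}, retention and follow-up.** For severe relugolix-related effects in general, "the principal investigator will decide whether to discontinue the trial or not". The liver is not named.
- **{11d}, concomitant care.** Under monitoring, "the study drug will be continued under supportive care". The permitted care includes "hepatotropic agents (ursodeoxycholic acid or stronger neo-minophagen C) for abnormal liver function", with no grade given.

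**The concern.** A stopping rule for liver injury should give the same answer wherever a physician looks it up. Here {11b} sets a numerical threshold, while {22} describes a decision that could go either way and that depends partly on what the patient wants. Nothing in {22} refers back to {11b}.

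The first thing at stake is the safety of a patient whose liver enzymes rise on the drug. The second is that different physicians should act alike. The trial is open-label ({17a}), so whoever uses the discretion knows the patient's arm. {18a} schedules laboratory tests before treatment, at 8 weeks and after 24 weeks, with others only if the physician sees a need. The 8-week result is therefore the one scheduled on-treatment liver check with dosing still to come (24 − 8 = 16 weeks). An unclear rule would matter most at that visit.

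**Working it through.** The article states no figure that bears on this point, so the check is a comparison of the texts.

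**Step 1: is the {11b} liver item discretionary?** Other items in the same list have judgement written in. Depression counts only after psychiatric treatment has failed and the drug is thought to be the main cause. Item 6 turns on whether continuing is inadvisable, and item 12 on the physician's view. The liver item has only its grade threshold and the introductory condition that the reaction be serious and drug-associated. Once that condition is met, the listed action is to discontinue.

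**Step 2: does the {22} decision reach the liver?** The phrase about the adverse reaction mentioned above follows directly on the depression sentence and is singular, so by itself it might mean depression only. The later sentence removes the doubt for the liver: "Although the frequency of hepatic dysfunction is not revealed but has also been reported, then the same measures will be taken". Those measures include the decision whether to discontinue.

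**Step 3: what does the {22} decision concern?** It weighs the patient's wishes, so it is about the individual and not about closing the whole study. Whether it concerns study drug, follow-up or both is not stated.

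**Step 4: apply the sections to drug-related AST/ALT by grade.**

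| Grade | {11b} | {22} | {11d} |
|---|---|---|---|
| 1 | No stop | Below the endpoint | Continue with liver agents; no conflict |
| 2 or 3 | Stop | Below the endpoint; the sentence on hepatic dysfunction names no grade, so the decision may apply | No grade named; agrees with {11b} if confined to below grade 2 |
| 4 | Stop | Safety endpoint; decision whether to discontinue | As for grade 2 or 3 |

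The grade 4 row holds the clear conflict: {11b} requires a stop, and {22} read literally allows continuation.

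**Step 5: what follows for the analysis?** The statistical methods in {20a} contain no primary or secondary test of the liver endpoint. The endpoint lies 4 − 2 = 2 grades above the stopping threshold, so events at grades 2 and 3 end treatment without counting in it. They would still be recorded as adverse effects at the monthly checks ({18a}) and notified to the data center as discontinuations ({19}).

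**The case against.** The best defence is that the sections have different jobs. {11b} is the specific rule for the allocated treatment. {22} and {18b} describe examination, specialist care, notification and reporting, and neither states that relugolix may go on after an {11b} criterion is met. A specific threshold would ordinarily govern over general text. Also, {11b} itself requires a judgement of seriousness and causality, and the decision in {22} could be where that is made. Finally, this is a condensed article, and the full protocol may set the order of precedence.

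Part of this stands. Judgement before the criterion is met is legitimate, and continuation under {22} is a literal reading, not an express permission. But {22} applies its decision to hepatic dysfunction, speaks of discontinuing, and does not subordinate itself to {11b}. Two printed rules that can give different answers are not merely a detail left to a fuller document.

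Several stronger readings are tempting, and the article does not support them:

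- **That {11d} contradicts {11b}.** Grade 1 elevation is also abnormal liver function, so the two can be read together. The missing grade calls for clarification only.
- **That {18b} is a second, independent liver conflict.** It never names the liver and covers it only as one kind of severe effect.
- **That angina is in the same position.** The reach of the {22} decision beyond depression is explicit only for hepatic dysfunction, so this is uncertain.
- **That a grade 4 endpoint contradicts a grade 2 stop.** An endpoint and a stopping threshold may differ.

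**Conclusion.** The concern holds as a conflict between {11b} and {22} over stopping for drug-related liver injury. It is plainest at grade 4. It rests on two readings: that the {11b} list directs the action once its conditions are met, and that the sentence in {22} extending the same measures to hepatic dysfunction includes the decision whether to discontinue. If the sponsor intends that decision to cover only follow-up, the conflict is one of wording, and the article still needs to say so.

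The size cannot be expressed as a number of patients. The article itself says that the frequency of hepatic dysfunction is not known, and no rate is assumed here. All 140 planned patients come under the rule, but that is enrolment and not an effect. A reader might infer that the non-inferiority result is at risk. The documents do not support this, since no planned primary or secondary test uses the liver endpoint. The point should be corrected for patient safety and consistent handling.

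**What to change.** 1. In {22}, state that relugolix stops whenever an {11b} criterion is met, and that the decision left to the physician and patient concerns only further treatment and continued follow-up. Use the same wording in the general sentence of {18b}.
2. As a clarification in {11d}, state that continuing study drug with liver agents applies only to AST/ALT below grade 2.
3. Optionally, tabulate AST/ALT of grade 2 or higher by grade and arm, because the grade 4 endpoint omits the grade 2 and 3 events that end treatment. This adds information and does not correct a contradiction. The grade 4 endpoint can stay as it is.

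The cost is a short amendment, submitted to the review board as {25} requires, and a notice to the treating physicians. The optional table uses data already collected. No extra visit, test or patient is needed.
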